### Electronic Data Collection and Management

Data will be stored in a database developed with the Research Electronic Data Capture system (56), which is hosted on the server of the University of São Paulo. This software developed at Vanderbilt University (TN, USA) is fully web-based and enables electronic data collection, management, and also study process management, while meeting the criteria set by the international policies on data privacy and security in the health sector (57).

### Sample Size Calculation

Most studies which aimed to assess the effects of non-invasive neurostimulation on cognitive function in TBI were case reports or small open labels studies. Moreover, there have been no previous studies comparing the cognitive effects of tDCS stimulation in patients with PPCS. Considering that there were no prior data on the effects of A-tDCS on patients with PPCS using our primary outcome measure, a formal sample size calculation was not possible; thus, we estimated that enrolling 30 patients would be a reasonable approach for an exploratory trial.

### Statistical Analysis

All analysis will be performed using Statistical Package for Social Sciences software version 23.0 for Windows (Prentice Hall, Chicago, IL, USA). A significance level of *p* < 0.05 will be considered for all tests. The quantitative variables will be described using the mean and SDs for normally distributed data or median with inter-quartile range for non-parametric data. The qualitative variables will be presented as absolute and relative frequencies. The five neuropsychological assessments will be summed and averaged to create a composite score. Cohen’s *d* will be calculated to compare the changes in the neuropsychological scores between the groups. An analysis of variance will be used to test whether there is an overall effect of any type of active stimulation on each outcome measure. When appropriate, we will perform *post hoc* paired comparisons using Bonferroni correction for multiple comparisons.

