#### Hopkins Verbal Learning Test (50)—Computer Version

This test consists of a list of 12 words. The computer program verbally reproduces the list at a 2-s interstimulus interval. Afterward, the patient is asked to recall as many items as possible in any order. Two additional learning trials are performed, and the delayed recall trial is conducted after a 25-min interval (51).

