#### Forward and Backward Digit Span

The computer version of the Wechsler Intelligence Scale for adults (WAIS III) (52) will be used. The digits forward test assesses attention and short-term memory, whereas the digits backward test measures working memory. A random number sequence is presented to the patient at a rate of approximately one number per second. At the end of each sequence, the patient must repeat the digits in the exact sequence (for the forward sequence) in which they were presented or in the opposite order (for the backward sequence). The test is stopped when the patient has consecutive failure on a sequence with the same digit span.

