#### Stroop Color–Word Test (53)

The Stroop test measures selective attention, cognitive flexibility, and processing speed. It consists of three cards presented by the examiner. The first card (word card) has 24 rectangles painted in brown, pink, blue, or green; the second card (color card) has 24 words (EACH, NEVER, TODAY, ALL) painted in brown, pink, blue, or green; the third card (color–word card) has 24 words (BROWN, PINK, GREEN, and BLUE) painted with mismatched colors. For each card, the subject is asked to say the name of the color as fast as he/she can. The score is calculated based on the time required to respond for each card.

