#### Corsi Block Test (Computerized Version) (53)

This test assesses visual–spatial short-term working memory. This test requires the subject to observe the sequence of blocks “tapped” (illuminated in the computer version) and then repeat the sequence in the same order. The task starts with a short sequence of blocks that gradually increases in number for up to nine blocks. The test measures both the number of correct sequences and the longest sequence remembered.

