#### Inhibitory Control Test (ICT)—Computerized Version (54)

This test assesses attention and inhibitory control of action. In this computerized test, the patient is shown a series of letters and is asked to press the backspace of the keyboard when the letter X is followed by the letter Y or if Y is followed by X. X and Y are the target letters; however, during the presentation of the series, other letters are included and serve as distracters. Patients are instructed not to respond to X following X or Y following Y. The ICT is administered as a practice test followed by a series of six similar 2-min trials separated by breaks to allow the subjects to rest. Performance is evaluated as the number of times the patient misses by clicking following an incorrect letter sequence (55).

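### As stated, the composite averages five tests that improve in opposite directions, so a uniform gain is at least partly cancelled in it

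*Protocol article*

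**What the plan says.** The Statistical Analysis section of the protocol article states: "The five neuropsychological assessments will be summed and averaged to create a composite score". The Instruments section describes exactly five tests that fit this sentence:

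- Hopkins Verbal Learning Test: "the patient is asked to recall as many items as possible in any order". Words recalled; higher is better.
- Forward and Backward Digit Span: "The test is stopped when the patient has consecutive failure on a sequence with the same digit span". The score unit is not spelled out, but getting further is better.
- Corsi Block Test: "The test measures both the number of correct sequences and the longest sequence remembered". Both are better when higher.
- Stroop Color–Word Test: "The score is calculated based on the time required to respond for each card". Lower is better.
- ICT: "Performance is evaluated as the number of times the patient misses by clicking following an incorrect letter sequence". A count of wrong responses; lower is better.

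The Statistical Analysis section also says that Cohen's d "will be calculated to compare the changes in the neuropsychological scores between the groups", and: "An analysis of variance will be used to test whether there is an overall effect of any type of active stimulation on each outcome measure". The article nowhere mentions z-scores, norm-based scores, reversed scoring or weights.

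**The concern.** A composite needs a common scale and a common direction. This rule supplies neither: it combines words, spans or sequences, response time and error counts, with three components rising and two falling as the patient improves. The score therefore has no defined good direction, and the test with the largest spread in its own units weighs most.

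The conflict touches the benefit that the trial hopes to see. The Primary Outcome Measures section predicts gains in episodic memory and executive function together, and the Study Purpose and Objectives section specifies executive function as inhibitory control. Better recall raises the Hopkins score and so the composite. Better inhibitory control lowers the ICT count and so lowers the composite. At stake is whether the one overall cognitive score that the plan defines can be read at all.

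**Working it through.** The article derives no figure for the composite, so there is none to reproduce. The check is direct arithmetic on the rule.

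**Inputs from the article.** Direction s = +1 for Hopkins, Digit Span and Corsi, and s = −1 for Stroop time and ICT errors; composite = sum of the five divided by 5.

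**Assumed inputs.** The article gives no SDs and no expected effect. Both are assumed below and varied.

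**Formula.** If every test truly improves by d of its own SD, then

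composite change = (d / 5) × [(SD_Hopkins + SD_Digit + SD_Corsi) − (SD_Stroop + SD_ICT)].

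The second bracket is always positive, so some of the gain is always lost. The change is zero when the brackets are equal and negative when the second is larger.

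| Case | d | Hopkins, Digit, Corsi SDs | Stroop (s), ICT SDs | Calculation | Composite change |
|---|---|---|---|---|---|
| A | 0.3 | 5, 3, 2 | 4, 3 | 0.3 × (10 − 7) / 5 | +0.18 |
| B | 0.3 | 5, 3, 2 | 6, 4 | 0.3 × (10 − 10) / 5 | 0.00 |
| C | 0.3 | 5, 3, 2 | 10, 5 | 0.3 × (10 − 15) / 5 | −0.30 |
| D | 0.3 | 5, 3, 2 | 20, 8 | 0.3 × (10 − 28) / 5 | −1.08 |
| E | 0.5 | 2.5, 2, 1 | 3, 2 | 0.5 × (5.5 − 5) / 5 | +0.05 |
| F | 0.5 | 2.5, 2, 1 | 8, 5 | 0.5 × (5.5 − 13) / 5 | −0.75 |
| G | 0.5 | 2.5, 2, 1 | 15, 8 | 0.5 × (5.5 − 23) / 5 | −1.75 |

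**As an effect size.** Divide the change by the composite's between-patient SD, √(Σ s_i s_j ρ_ij SD_i SD_j) / 5, where ρ is the correlation between tests once all are oriented the same way. For ρ from 0 to 0.4:

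- A: +0.11 to +0.14
- B: 0
- C: −0.12 to −0.14
- D: −0.24 to −0.26

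These use the SD of the score, not of within-patient change, so they serve only for comparison with each other and with the corrected score below.

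**Weight of single tests (ρ = 0).** Stroop alone carries 16/63 = 25% of the composite's variance in A and 400/502 = 80% in D.

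**One invented patient.** Hopkins, Digit Span, Stroop, Corsi and ICT go from 22, 14, 25, 10, 8 to 24, 15, 21, 11, 6. All five improve. The composite goes from 79/5 = 15.8 to 77/5 = 15.4.

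**Standardising without reversing.** Only (3 − 2)/5 = 20% of the gain survives: 0.3 becomes 0.06.

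**Standardising and reversing.** The composite change is +0.30 whatever the SDs. The effect size is 0.3 / (√5/5) = 0.67 at ρ = 0 and 0.3 / (√13/5) = 0.42 at ρ = 0.4.

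**The case against.** The best defence is that the article never says raw scores are added. It names neither the score that each test contributes nor the form in which it enters, and scaling and orientation are details that an analysis plan not shown here may supply. That is fair as far as it goes: the raw sum is the literal reading, not the article's word. But sum-and-average is a stated rule and the only operation given. Followed as it stands, it yields a score without a direction, so the point is more than missing detail.

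The defence is right on reach. A reader might infer that the main result of the trial is compromised, particularly because the Sample Size Calculation section speaks of a primary outcome measure in the singular without identifying it. The documents do not support that step. The primary hypothesis is framed on episodic memory and executive function, the composite is not named as primary, and the analysis of variance is applied to each outcome measure. Those per-test results are untouched, and a composite pointing the wrong way would be visible beside them.

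The defence is also right on size. A reader might infer that the composite will show a true benefit as harm, or that Stroop is bound to dominate it. Both depend on SDs that the article does not give; cases A and E stay positive. Partial cancellation of a uniform gain is certain under the literal rule, while a reversed sign is only possible. The variance shares further assume uncorrelated tests, which is unlikely for five cognitive tests in the same patients.

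**Conclusion.** The point holds for the composite alone. Under the stated rule, an equal improvement on all five tests is always partly cancelled. It appears as a decline when the Stroop and ICT SDs together exceed the Hopkins, Digit Span and Corsi SDs together. The directions and units come from the article, whereas every magnitude above rests on assumed SDs and an assumed uniform effect. Since the trial is described as exploratory, the composite is not named as primary, and the per-test analyses of variance and effect sizes stand, this should be fixed but does not undermine the trial's main analyses.

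**What to change.** Before unblinding, replace the composite sentence with a definition in four parts:

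1. Name one score per test. Four tests offer a choice: Hopkins (learning trials or delayed recall), Digit Span (forward or backward), Stroop (three card times) and Corsi (correct sequences or longest sequence). The article does not settle these. The choice is one of substance for the investigators and should be on record before results are seen.
2. Convert each score to a z-score using the mean and SD of all patients at the session 1 pre-stimulation assessment, and keep that reference for every later assessment.
3. Multiply Stroop time and ICT errors by −1 so that higher is better throughout.
4. Define the composite as the mean of the five z-scores.

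The cost is a few sentences and one decision on scores. No new data, visits or tests are needed, and the per-test analyses do not change.

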**Figure 1 F1:**
[figure not shown]
**Fluxogram of the study**.

All the subjects will receive all types of stimulation (L-DLPFC, L-TC, or Sham). The interval between each session will be 7 days to avoid carry-over effects. Because this is a crossover study, all participants will receive all proposed stimulation sessions. A computerized neuropsychological test will be performed before and immediately after each stimulation session.

(A)Frontal stimulation: patients will receive A-tDCS over the L-DLPFC at an intensity of 1.5 mA for 20 min.(B)Temporal stimulation: patients will receive A-tDCS over the L-TC at an intensity of 1.5 mA for 20 min.(C)Sham stimulation: patients will receive sham stimulation over the occipital area for only 30 s, after which the current will be turned off automatically without the patient’s knowledge. To guarantee blinding to the stimulation parameters, the A-tDCS electrode will be placed over the occipital region to simulate a study protocol using three different stimulation positions.

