### Randomization and Blinding

Randomization will be done *via* a computer-produced randomized controlled table. All the 20 patients will be randomized into the three types of stimulation: frontal stimulation, temporal stimulation, and sham stimulation. The neuropsychologists and the patients will be blinded for the type of stimulation performed in each session.

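### The analysis section describes a three-period crossover in parallel-group terms, fixes no patient or session term, and does not use the pre-session score as a covariate

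*Protocol article*

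**What the plan says.** The Procedure section is clear about the design: "Because this is a crossover study, all participants will receive all proposed stimulation sessions". It spaces the three sessions a week apart ("The interval between each session will be 7 days to avoid carry-over effects") and measures at both ends of each one: "A computerized neuropsychological test will be performed before and immediately after each stimulation session".

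Statistical Analysis then uses other language. Cohen's d "will be calculated to compare the changes in the neuropsychological scores between the groups", and "An analysis of variance will be used to test whether there is an overall effect" of active stimulation on each outcome. Follow-up tests are called paired and are Bonferroni-corrected. The section names no patient, session or sequence term. It does not say whether the outcome of the analysis of variance is the change or the post-session score.

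On size, the Sample Size Calculation section says "we estimated that enrolling 30 patients would be a reasonable approach for an exploratory trial" and gives no effect size, SD or correlation.

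**The concern.** A three-condition crossover has no treatment groups; it has one set of patients seen three times. An effect size and an F test described as if there were groups can be carried out in ways that give different standard errors, and the text does not choose between them.

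Session matters as well. Three sessions with a test before and after each make 3 × 2 = 6 administrations, besides the baseline neuropsychological assessment. A week between sessions is aimed at carry-over of stimulation. It does not remove learning of the tests. Unless session is in the model, any drift goes into the error term or, if the orders are unequal, partly into the stimulation contrasts.

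The trial also collects a pre-session score each time. Subtracting it is one use of it, but usually not the most precise one. With 30 patients and no formal sample size calculation, precision is worth protecting.

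**Working it through.** **Inputs from the article.** 30 patients, 3 conditions per patient, a pre- and a post-score at each session, significance level 0.05 (taken as two-sided). The article has no power figure to reproduce.

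**Assumed inputs.** The correlation ρ of the analysed score across sessions, the within-session pre/post correlation r, the effect size and the practice drift. None is documented, so ranges are shown.

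**Step 1: leaving out the patient.** With SD 1, the standard error of a pairwise difference is √(2/30) = 0.258 if the conditions are treated as separate groups, and √(2(1−ρ)/30) within patients. At ρ = 0.5 the latter is √(1/30) = 0.183. The ratio is 1/√(1−ρ). Simulated results for the overall F test (N = 30, balanced orders, one condition shifted by 0.5 SD of the analysed score, no practice drift) are:

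| ρ | SE ratio | Type I error, one-way | Power, one-way | Power, patient + session |
|---|---|---|---|---|
| 0 | 1.00 | 5.1% | 50% | 49% |
| 0.3 | 1.20 | 1.4% | 46% | 64% |
| 0.5 | 1.41 | 0.3% | 42% | 79% |
| 0.7 | 1.83 | 0.0% | 39% | 95% |

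For positive ρ the error is conservative. Only a negative ρ would reverse it (ratio 0.88 at ρ = −0.3).

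**Step 2: leaving out session.** Take ρ = 0.5 and a drift of 1 SD in the analysed score over the three sessions. An analysis with patient but not session has type I error 1.0% and power 59%; adding session gives 5.0% and 79%. With randomly drawn orders, power is 61% against 78%, and type I error is close to 5% either way.

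**Step 3: when the outcome is change.** Subtracting the pre-session score removes stable patient differences, and also any practice shift that is equal before and after the session. If changes are then uncorrelated across sessions, ρ in Step 1 is near 0. Simulation with a 0.4 SD benefit, a between-patient share of variance of 0.6 and additive practice effects gave power of 39–40% one-way, 38–40% with patient, and 38–39% with patient and session. One-way type I error was 4–5%. Leaving out patient and session then costs almost nothing.

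**Step 4: change against covariate adjustment.** Let pre and post have within-patient variance σ² and correlation r once patient is removed. Change has variance 2σ²(1−r); the adjusted post-score has σ²(1−r²). The ratio is 2(1−r)/[(1−r)(1+r)] = 2/(1+r): 2.0 at r = 0, 1.33 at 0.5, 1.18 at 0.7 and 1.11 at 0.8. For N = 30, a 0.4 SD effect and changes uncorrelated across sessions, simulated power is:

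| r | One-way on change | Post-score with patient, session, pre-score |
|---|---|---|
| 0 | about 39% | 68% |
| 0.25 | 51% | 69–75% |
| 0.5 | 70% | 83% |

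**The case against.** The article nowhere says one-way or independent groups. Analysis of variance includes the repeated-measures form, the follow-up tests are called paired, and the crossover is stated plainly elsewhere. A condensed article may leave model terms to a fuller document. A randomised comparison of change is unbiased, the trial is exploratory, and where the standard error is wrong with positive ρ it errs on the safe side.

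Most of this stands. Three stronger readings are therefore not supported:

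- A reader might infer that the 90 results (30 × 3) will be analysed as independent and that power collapses. The text leaves the model open. The large losses in Steps 1 and 2 apply only to a score that correlates across sessions or drifts; they do not describe an analysis of change scores uncorrelated across sessions.
- A reader might infer that the pre-session score is ignored. It is not, because a change subtracts it. What is absent is adjustment for it as a covariate.
- A reader might infer from "This test consists of a list of 12 words" that one word list is reused at every administration. That sentence describes the format of the test and says nothing about alternate forms.

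What the objection does not remove is the group wording, which stands in the article itself and does not fit the design. Nor does the word paired rescue it: it may mean within-patient or merely pairwise. On the favourable reading, the paragraph sets within-patient follow-ups beside a between-group effect size and a test with no patient term.

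**Conclusion.** The point holds as a misdescribed and underspecified comparison with a clear, inexpensive improvement. It is not a demonstrated bias or a risk of false positives.

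The size is conditional. If patient and session are omitted and the analysed score correlates 0.5 across sessions, standard errors are 1.41 times too large. If the analysed score is a change uncorrelated across sessions, that loss is close to nil, and what remains is the inefficiency of raw change: 2.0-fold in variance at r = 0, 1.33-fold at r = 0.5 and 1.11-fold at r = 0.8. In the simulated settings of Step 4, the recommended model gains about 13 to 29 percentage points of power (83 − 70 and 68 − 39). The gain shrinks as r rises.

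All of this rests on assumed correlations, an assumed effect and N = 30. The Randomization and Blinding section gives a different number ("All the 20 patients will be randomized into the three types of stimulation"). That conflict is a separate matter to be reconciled.

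**What to change.** Replace the analysis of variance with a within-patient model of the post-session score: stimulation, session (1, 2, 3) and that session's pre-session score as fixed effects, and patient as a random (or fixed) effect. Report each stimulation contrast as an adjusted within-patient difference with a 95% CI. Accompany it with a standardised effect computed from that within-patient difference, with its denominator named, in place of d between groups. State that the Bonferroni-corrected follow-ups are contrasts from this model.

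The cost is small. With patient fixed, residual degrees of freedom go from 90 − 30 − 2 = 58 (patient and stimulation only) to 58 − 2 − 1 = 55 once session and the pre-score are added. Beyond that there is a change of wording and slightly more programming. No new data are needed, since every pre-session score is already collected.

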### Ethical Issues

Considering the study’s context and design, there will be minimal risk to patients. Non-invasive neuromodulation techniques follow the ethical criteria for studies involving human participants by respecting the principles of autonomy, beneficence, non-maleficence, and proportionality to ensure that the subject will not be harmed if he/she participates in the study.

Transcranial direct current stimulation can be considered a safe intervention for several reasons: (A) the electric current applied is very low (1–2 mA over an area of 25–35 cm^2^), (B) there is no direct contact between the electrodes and the brain, and (C) the electrodes are embedded in a saline solution, minimizing tissue resistance and avoiding overheating (58–60).

The most common adverse effects observed in safety studies were tingling sensations, itching, mild transient redness of the skin and discomfort on the site of stimulation, moderate fatigue, difficulty concentrating, nausea, and headache. However, these effects were short-lived and were presented at the same frequency between the experimental and placebo groups (60). Patients will be queried after each tDCS session as to whether they experienced adverse effects and how these effects were related to the tDCS treatment. Stimulation sessions have been established by [name] [name], Assistant Professor in the Division of Psychiatry of HC-FMUSP, who will provide any assistance if necessary.

Several advantages of tDCS have been highlighted in clinical practice. These advantages include few side effects that are usually benign, high tolerability, and good potential for efficacy. Notably, it has been emphasized that this technique “has been used in several clinical trials in the last decade and to date, no serious adverse effect has been reported” (58).

